### Design

A 24-week cross-over design trial will compare a Mediterranean diet intervention with a low-fat diet intervention. Each participant will complete both dietary interventions for 8 weeks and the two intervention phases will be separated by an 8-week washout period (See Fig. 1). An independent staff member of the SIHR will perform the block randomisation procedure. Participants will be allocated to one of two groups using, stratified by age and gender, to determine the order in which they undertake the interventions. Allocation concealment will ensure that study personnel and volunteers are not aware of the starting intervention prior to enrolment. During the washout period participants will return to their habitual diet to prevent cross-contamination of effects between dietary phases.

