### Dietary interventions

Neither diet will restrict energy intake. Instead, participants will be advised to self-regulate their food intake and consume foods ad-libitum.

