#### Low-fat diet

Guidelines for the low-fat diet are based on the PREDIMED study, which compared two variations of a Mediterranean diet with a low-fat control diet [45]. Participants will be advised to make adjustments to their habitual diet in order to reduce total fat intake. Specifically, high fat foods, including all types of oil, butter, margarine, processed and high fat meats, nuts, chocolates, cakes, pastry, and high or full fat dairy, will be replaced with low-fat alternatives, such as breads and cereals, legumes, rice, fruits and vegetables and low-fat varieties (e.g. low-fat dairy, low-fat sauces). Daily limits will be set for oil (no more than 20 ml), butter and margarine (no more than two teaspoons), and participants will be instructed to remove visible fat and skin from meat and fish before cooking.

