#### Secondary outcome measures and covariates

Over the four assessment time points, home measured diastolic blood pressure and heart rate, clinic blood pressure and heart rate, BMI, waist-to-hip ratio, body composition, fasting blood lipids, C-reactive protein (CRP), fasting plasma glucose, fasting serum insulin, erythrocyte fatty acids, cognitive function, psychological health and well-being, and dementia risk will be examined as secondary outcomes.

Clinic blood pressure will be measured using an Omron Healthcare Co. digital blood pressure monitor (model 1A1B Hem-7000-CIL). The same protocol as for home blood pressure measurement will be followed, where participants will be seated for 5 min and three measurements will be taken spaced at least 1 min apart. Waist and hip circumference will be measured to determine waist-to-hip ratio. Body composition, including percentage body fat, lean mass and abdominal adiposity will be measured using dual-energy x-ray absorptiometry (DEXA). Fasting venous blood will be collected through venepuncture and analysed at an external NATA accredited laboratory using standard procedures. Erythrocyte fatty acids will be measured using direct transesterification as described by Tu et al. (2013) once further funding has been secured. Whole blood will be centrifuged (4 °C, 4000 rpm, 10 min) to separate erythrocytes from spare plasma, both of which will be frozen at −20 °C and then stored at −80 °C. APOEε4, an indicator of increased risk for AD, will be determined using the TaqMan® SNP Genotyping assay kit (Applied Biosystems, Warrington, UK) [50]. For explorative purposes, a faecal sample will also be collected to examine the effects of a Mediterranean diet on gut microbiota. Faecal samples will be frozen at −20 °C and then stored at −80 °C until further funding has been secured.

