The primary analysis will be performed on a per protocol basis including only those subjects who complete both trial phases. A linear mixed effects model will determine the difference in each outcome between dietary interventions and will measure both between and within subject effects for cardiometabolic and cognitive outcomes. If a significant change is detected for cognitive outcomes a hierarchical regression will include cardiometabolic outcomes to assess their meditating effects. A sensitivity analysis will include weight loss, change in physical activity, medications and supplements as these may cause time-varying confounding should they differ between groups in the second dietary phase. Further, carryover and treatment-period effects will be assessed by including treatment*phase and treatment*order interaction terms. A diet*period*energy intake interaction term will be included to determine any significant changes between diets in relation to total energy intake, macronutrient intake and micronutrient intake. As an additional sensitivity analysis we will also include subjects that did not complete the trial or were not included in the per protocol analysis due to inadequate adherence (<75%). For missing data the linear mixed effects models will estimate unbiased effects as opposed to multiple imputation.

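### The diet*period*energy intake term cannot show whether intake differs between diets, because intake is a covariate in that model and not the response

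*Protocol article*

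**What the plan says.** All the model terms at issue are in the Statistical analysis section of the protocol article. A linear mixed effects model estimates the difference in each outcome between diets. On dietary intake the plan says: "A diet*period*energy intake interaction term will be included to determine any significant changes between diets in relation to total energy intake". The sentence goes on to name macronutrient and micronutrient intake. Just before it, the plan says that "carryover and treatment-period effects will be assessed by including treatment*phase and treatment*order interaction terms".

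On weight, the same section says: "A sensitivity analysis will include weight loss, change in physical activity, medications and supplements as these may cause time-varying confounding". It adds a condition, namely that these variables differ between the groups in the second phase.

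The design that these terms must fit is in the Design section: "Each participant will complete both dietary interventions for 8 weeks". Randomisation to one of two groups serves "to determine the order in which they undertake the interventions". Under Dietary interventions energy is unrestricted and "participants will be advised to self-regulate their food intake and consume foods ad-libitum". Participants on the control diet are told to "make adjustments to their habitual diet in order to reduce total fat intake". The secondary outcomes include "BMI, waist-to-hip ratio, body composition, fasting blood lipids, C-reactive protein (CRP". Under Dietary adherence, three-day weighed food records are planned before and at the end of each diet phase.

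**The concern.** Whether intake differs between diets is a question about intake, so intake has to be the response. The plan puts it on the other side of the equation, as part of a three-way interaction in a model for something else. The p-value from that term would be reported as the answer to a question it does not address. The diets could differ clearly in energy or nutrients and the term would stay silent. It could also be significant when intake is the same on both diets. Diet composition is the intervention here, so a reader will want a sound comparison of nutrient intake.

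The secondary matter is how weight loss is described. Weight is measured after randomisation, the diets may change it, and BMI and body composition are themselves outcomes. If part of a diet effect on blood pressure runs through weight, adjusting for weight removes that part. Calling the adjusted model a check for confounding invites the reading that a smaller estimate weakens the main result.

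**Working it through.** The plan states no figure on this point, so there is none to reproduce. The check has three parts.

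**1. What the term tests, with period read as phase.** Code diet +1 for Mediterranean and -1 for low-fat, phase -1 for first and +1 for second, and order +1 for Mediterranean first and -1 for low-fat first.

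| Order group | Phase | Diet | Diet × phase | Order | Diet × order |
|---|---|---|---|---|---|
| Mediterranean first | -1 | +1 | -1 | +1 | +1 |
| Mediterranean first | +1 | -1 | -1 | +1 | -1 |
| Low-fat first | -1 | -1 | +1 | -1 | +1 |
| Low-fat first | +1 | +1 | +1 | -1 | -1 |

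In every row diet × phase = -order and diet × order = -phase. A matrix with intercept, diet, phase, order, diet × phase and diet × order therefore has rank 4 with 6 columns. Multiplying by intake gives diet × phase × intake = -(order × intake). The coefficient measures whether the slope of the outcome on intake differs between the two order groups.

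**2. How the term behaves.** The simulation used 31 participants (the target sample size), a two-sided 5% level (Statistical analysis) and 3,000 runs per setting. The model was generalised least squares with a random participant intercept. These values are assumed and are not in the document:
- blood pressure SD 7.7 mmHg between and 5 mmHg within participants;
- intake SD 1.2 MJ between and 1.0 MJ within participants;
- outcome slope 2 mmHg per MJ;
- direct diet effect -2.5 mmHg.

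Share of runs with p < 0.05:

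| True situation | Diet × period × intake | Diet × intake | Intake as response, diet effect |
|---|---|---|---|
| No intake difference | 4.3% | 4.9% | 4.4% |
| Intake differs by 1 MJ | 5.1% | 5.1% | 97.5% |
| Intake differs by 2 MJ | 4.7% | 4.9% | 100% |
| Equal intake, slope differs by order | 71% | 4.9% | 5.0% |
| Equal intake, slope differs by diet | 4.5% | 97% | 4.9% |

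In the last two rows the slopes were 2 + 2 = 4 and 2 - 2 = 0 mmHg per MJ, a deliberately large contrast.

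The 97.5% can be checked by hand. The standard error of the within-participant diet difference is 1.0 × √(2/31) = 0.254 MJ, and 1/0.254 = 3.94 standard errors. With a critical value near 2.0, power is about 97%. The simulated intake model had diet, phase and participant. Order, which the fix adds, is a between-participant term.

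So the three-way term ignores intake differences and responds to slope differences by order. It also misses effect modification by diet, for which diet × intake is the right term.

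**3. Adjusting for a variable that the diet changes.** In the same simulation the total diet effect with a 1 MJ reduction is -2.5 + 2 × (-1) = -4.5 mmHg by construction. The unadjusted model returned -4.54 and the intake-adjusted model -2.56. With 2 MJ the figures were -6.47 and -2.46. The adjusted estimate recovers the direct part only. The same logic applies to weight. The sizes follow entirely from the assumed slope and intake change, so they show direction and nothing more.

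**The case against.** Several objections have force.

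- **The meaning of period.** The plan uses both phase and period, and there are four assessments, at weeks 0, 8, 16 and 24. If period means before versus after within a phase, diet × period is a diet-by-time effect and not order. The term would then ask whether diet-related change varies with intake. The phrase on treatment-period effects in the sentence before favours the phase reading but does not settle it. This stands as a limit on the aliasing result. It does not rescue the term, because intake is still a covariate under either reading.
- **Weight and the primary model.** A reader might infer that the primary estimate is distorted by weight adjustment. It is not: weight loss enters only a sensitivity analysis.
- **The confounding label.** A reader might reject that label for every variable in the sentence. The document does not support this. Participants are told to keep exercise and medications as usual, so changes in them are departures from instruction. The primary set is also restricted to completers, with an adherence rule. Weight lost in the first phase and not regained in washout could carry into the second. The criticism therefore applies to weight loss alone.
- **Whether the diets change weight.** This is expected, not shown. The bi-weekly weighing and dietitian follow-up may limit it. On the other side, the Background counts weight and BMI among cardiometabolic markers that pork substitution may improve, and the analysis section elsewhere treats cardiometabolic outcomes as possible mediators.
- **Reach.** Nutrient intake is not a listed outcome, and the article condenses a fuller protocol. One cannot conclude that intake will be compared nowhere else. The point is about the analysis that this article states.

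**Conclusion.** The point holds as a mismatch between a stated analysis and its stated purpose. The three-way term cannot show whether energy, macronutrient or micronutrient intake differs between diets, and this does not depend on how period is read. If period is phase, the term is order × intake and tests only whether the outcome-intake slope differs by order. Under the assumed variances its rejection rate stayed between 4.3% and 5.1% whether intake differed or not.

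The secondary point holds for weight loss only. Weight is measured after randomisation, may respond to ad-libitum diets and underlies listed secondary outcomes, so the adjusted estimate does not check the total diet effect for confounding.

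It would be tempting to state how much the blood pressure effect would shrink. For example, assuming that 1 mmHg of the 2.5 mmHg target difference runs through weight gives 1/2.5 = 40%. That figure only repeats the assumption, and the document gives no mediated share. Neither point touches the primary model for home systolic blood pressure or the sample size.

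**What to change.** 1. Delete the diet*period*energy intake term.
2. Analyse energy, macronutrient and micronutrient intake from the weighed food records as outcomes in the same kind of mixed model, with diet, phase and order as fixed effects and participant as random. The diet coefficient then answers the stated question. With order in the model, a diet*phase term should not be added as well, since with one end-of-phase record per phase the two are the same column.
3. If effect modification by intake was intended, say so, use diet*intake, and label it exploratory because intake is measured after randomisation.
4. Take weight loss out of the confounding sensitivity analysis and report the weight-adjusted model as an exploratory direct-effect analysis beside the unadjusted total effect. Physical activity, medications and supplements can stay where they are.

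The cost is a change of wording in the analysis section. No new data are needed, because the food records and weights are already planned.

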### Trial and data management

To ensure privacy and confidentiality each participant will be assigned a unique study identification (ID) number. All source documents will be de-identified (re-identifiable by coded ID numbers) and stored in an individual file for each study participant. All information collected as part of the study will remain confidential and no information that could lead to identification of any individual will be released. Access to trial data will be limited to the team of investigators named as authors on this publication.

Unintended effects and adverse events of the trial intervention will be identified during bi-weekly dietetic visits. All adverse and serious adverse events will be recorded and serious adverse events will be reported by the Chief Investigators to the University of South Australia Human Research Ethics Committee. Participants will be advised to consult with their General Practitioner regarding any notable symptoms identified throughout the trial. If the instance of adverse events a decision to continue, modify or cease the intervention will be made on a case-by-case basis.

Due to the size of the trial and nature of the trial intervention a Data Monitoring Committee is not deemed necessary. The Chief Investigator will conduct quality control checks of data values twice during each dietary intervention phase to ensure data quality.

Electronic data entry will be completed throughout the trial by study personnel. Electronic data files will be stored on a secure password protected network and backed up regularly on an external hard drive. Once the trial is complete and results have been published electronic files will be stored on a DVD in the Sansom Clinical Trials facility secure data store in the Bonython Jubilee Building, City East Campus. Study documentation will be kept in locked filing cabinets within in the Sansom Clinical Trials facility in the Bonython Jubilee Building, City East Campus. Once the study is complete and results have been published all data will be archived and stored for a total of 15 years.

Any changes to the trial protocol will require approval by all authors and the University of South Australia Human Ethics Committee. Once approved, modifications to the trial protocol will be communicated to the funding sponsors and the journal wherein the protocol is published.

Results from this trial will be disseminated through peer-reviewed international journals, presentations at national and international meetings and the lead author’s doctoral dissertation. Participants will be provided with a copy of their personal results within 6 months of completing the study and a summary of the research findings will be sent to all participants once data analysis has been completed.

## Discussion

To reduce the impact of both dementia and CVD health and lifestyle interventions with the potential to mitigate multiple risk factors have been recommended above reactive, costly treatments [71, 72]. Risk factors such as hypertension, dyslipidaemia, insulin sensitivity are shared by both dementia and CVD [73–76]. Interventions targeting each of these simultaneously may be effective in reducing the prevalence of both CVD and dementia. However, it is necessary to ensure that such interventions are sustainable, both for the target population and the environment.

The Mediterranean diet has demonstrated efficacy for reducing risk of CVD and cognitive decline. Yet an Australian population, who typically consumes a high quantity of meat, may find adhering to the meat restrictions of the diet difficult. This paper outlines the protocol of a randomised controlled trial that endeavours to compare a Mediterranean diet with an additional source of meat protein, against a low-fat control diet. Findings of the forthcoming study will be relevant at a policy, clinical and individual level and will provide insight as to whether consuming pork as a part of a Mediterranean diet can improve health outcomes while simultaneously increasing variety and sustainability for the target population.

## Abbreviations

ACE-R: Addenbrooke’s cognitive examination – revised
ATS: Attention switching task
BMI: Body mass index
CAIDE: Cardiovascular risk factors, aging and dementia
CANTAB: Cambridge automated neuropsychological test automated battery
CRP: C-reactive protein
CVD: Cardiovascular disease
DEXA: Dual-energy x-ray absorptiometry
DLQ: Diet and lifestyle questionnaire
DMS: Delayed matching to sample
EEG: Electroencephalography
EPIC: European prospective investigation into cancer
EVOO: Extra virgin olive oil
FRS: Framingham risk score
HDL: High-density lipoprotein
ID: Identification
KSS: Karolinska sleep scale
LDL: Low-density lipoprotein
MCI: Mild cognitive impairment
MOT: Motor orientation task
NATA: National Association of Testing Authorities, Australia
OTS: One touch stockings of cambridge
PAL: Paired associates learning
POMS: Profile of mood states
PREDIMED: Prevención con Dieta Mediterránea
RCT: Randomised controlled trial
RTI: Reaction time
RVP: Rapid visual information processing
SF-36: Short form-36 health survey
SIHR CTF: Sansom Institute for Health Research Clinical Trial Facility
SWM: Spatial working memory
T2DM: Type 2 diabetes mellitus
VAS: Visual analogue scale
VRM: Verbal recognition memory
WFR: Weighed food record
